### 2.4. Sample size

Based on a previous study performed by our team members (26), and to find a 20% difference between the percentage of patients in abstinence (partial or total) between EG (37%) and CG (20%), for an alpha error of 5%, and statistical power of 80%, the size would be 220 subjects (110/group). Since it is a cluster randomization system, we will consider the “design effect” and we will assume a loss rate of 5%. Estimates of the intra-cluster correlation coefficient (ICC) in ECC by clusters in PC show that they are generally less than 0.05 (27). This ICC translates, for a cluster size of 15, into a design effect corresponding to a factor of 1.7. Assuming this value, the size would be 394 subjects to recruit (197 in each group).

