#### 2.1.3. Random assignment

The randomization unit will be the healthcare professional, and the intervention unit will be the patient. Professionals will be randomly assigned and equally (1:1) to one of the two study groups (EG or CG), stratifying according to the center and type of professional. Patients will be recruited through consecutive sampling (opportunistic search of subjects who are treated at participating health centers).

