### 2.3. Statistical analysis

An intention-to-treat analysis will be performed to control the effects of losses and dropouts, dragging for analysis the data from the last observation obtained. Survey data will be automatically processed on Google Drive, directly by each of the participating researchers. They will then be exported to an Excel sheet from Google Drive and statistically treated with the SPSS v. 17.0. A descriptive analysis and an initial comparability analysis of the groups will be conducted. Confidence intervals of 95% will be calculated for the major study estimators. A bivariate analysis will be conducted to assess the relationship of the independent variables and the effect of the intervention, for which the Chi-square test will be used, the mean comparison test for independent samples, such as Student *t* test or ANOVA (after verification of normality by using the Kolmogorov-Smirnov test); bilateral comparisons were used, and a value of *p* ≤ 0.05 will be considered. A multivariate analysis will then be performed to determine which sociodemographic, work, and care factors are associated with the intervention developed, controlling the predictors and/or confounders by multiple linear regression and unconditioned binary logistic regression.

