**-Variables measured in patients with risky alcohol use:**

To assess the effectiveness of interventions, the main outcome variables will be the number of SDU in a typical day, the frequency of more than 6 SDU/day, and the total score of the AUDIT (21) questionnaire. All these variables will be considered as primary outcomes.

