### 3.1. Strengths and limitations

#### 3.1.1. Strengths

It is one of the first research studies with a randomized, two-arm, comparative clinical trial design that assesses the impact of MI under real clinical conditions (effectiveness rather than efficacy study) in the field of PC in patients with risky alcohol consumption, giving it a more practical character and immediate clinical applicability, as its external validity increases. In the current literature, there are studies focused on risky alcohol consumption and its health impact (12), which assess the efficacy (i.e., under ideal or “laboratory” conditions) of MI. But none designed to compare the brief motivational intervention delivered by an EG and the health advice based on the PAPPS recommendations provided by a CG, in the framework of daily consultations in PC.

At the same time, the study may show whether or not there are differences in outcome between two types of interventions: MI-based versus most commonly used (simple health advice) in this type of problem where a change in behavior or health habit is attempted.

The approach is focused on MI as an intervention on the patient with risky alcohol consumption, not only in the preventive phase, but throughout the whole process (the patient is not going to be only a passive subject receiving an intervention, but an active person–empowered–able to decide/perform therapeutic activities to prevent/treat their dependence with the aim of reducing their consumption or achieving abstinence).

The present study will quantify the level of effectiveness of the therapeutic intervention as a percentage of successes (people who reduce their consumption/achieve abstinence), an aspect that is poorly evaluated and which greatly affects the achievement and maintenance of proposed functional objectives and patient satisfaction with the healthcare professional-patient relationship presented throughout the management of risky alcohol consumption, this has not been evaluated to date for this health problem.

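### The 80% power in section 2.4 belongs to partial or total abstinence, which section 2.5.1 does not list as an outcome; power for the declared patient primaries is not established

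*Protocol article*

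**What the plan says.** Section 2.4 (Sample size) of the protocol article takes its rates from a previous study by team members. The trial is sized "to find a 20% difference between the percentage of patients in abstinence (partial or total) between EG (37%) and CG (20" per cent). It continues: "for an alpha error of 5%, and statistical power of 80%, the size would be 220 subjects (110/group"). That figure is then inflated for clustering (ICC 0.05, cluster size 15, design effect 1.7) and for dropout ("we will assume a loss rate of 5" per cent), giving 197 per group and 394 in all. The abstract repeats the same endpoint, rates and sizes.

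Section 2.5.1, on patients, says that "the main outcome variables will be the number of SDU in a typical day, the frequency of more than 6 SDU/day", together with the total AUDIT score, and states that all three are primary. The abstract names the primaries as self-reported level of alcohol use and AUDIT score. The primaries that 2.5.1 lists for professionals concern interview skills, the relationship with the patient, and awareness and attitude. Abstinence is not in 2.5.1 or in Table 1, and no section defines its partial form.

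The nearest other text is in section 3.1.1 (Strengths), which says that effectiveness will be quantified "as a percentage of successes (people who reduce their consumption/achieve abstinence").

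**The concern.** A power statement holds for one endpoint, one effect and one test. Here the endpoint that fixed the number of patients is not declared as an outcome, and the declared patient primaries have no design assumptions. A reader who takes 80% as the chance of detecting a worthwhile effect on AUDIT or SDU has no basis in the article for doing so. A null result on AUDIT could not be set against a planned detectable difference, and a positive abstinence result would concern an endpoint that the outcome section does not name.

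The article states both the sizing endpoint and the primary outcomes in full, and they do not match. A separate analysis plan could add a derivation, but sections 2.4 and 2.5.1 would still disagree.

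**Working it through.** **Inputs from the protocol article.** Rates 0.37 and 0.20, alpha 0.05, power 80%, loss 5%, ICC 0.05, cluster size 15, design effect 1.7 and final size 394 (section 2.4). Two-sided tests: "bilateral comparisons were used" (section 2.3). Equal allocation: "Professionals will be randomly assigned and equally (1:1) to one of the two study groups (EG or CG") (section 2.1.3). At least 50 professionals with 7 to 8 patients each (section 2.1.1.1).

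**Step 1: reproduce the plan's figure.** Two-proportion formula with pooled variance under the null and no continuity correction; mean rate (0.37 + 0.20)/2 = 0.285:

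n = [1.960 × √(2 × 0.285 × 0.715) + 0.842 × √(0.37 × 0.63 + 0.20 × 0.80)]² / 0.17² = 109.5, so 110 per group.

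Design effect = 1 + (15 − 1) × 0.05 = 1.70. Then 110 × 1.70 / 0.95 = 196.8, so 197 per group and 394 in total. The arithmetic is sound for its stated endpoint. It matches the 17-point gap between 37% and 20%; a true 20-point gap (40% against 20%) would give 82 per group.

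**Step 2: look for the same inputs for the declared primaries.** Sections 2.4 and 2.5.1 give no target difference, SD or event rate for SDU on a typical day, frequency of more than 6 SDU in a day, or AUDIT total. Power for these cannot be computed from the article.

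**Step 3: what 394 patients could detect.** Assumption: the outcome is analysed as a difference in means, without gain from baseline adjustment. Evaluable per group: 197 × 0.95 = 187.15.

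- At the stated design effect of 1.7, effective n = 187.15 / 1.7 = 110.1 per group.
- At the planned cluster size, 394/50 = 7.88 recruited and 7.88 × 0.95 = 7.49 evaluable per professional. Design effect = 1 + (7.49 − 1) × 0.05 = 1.324, and effective n = 187.15 / 1.324 = 141.3 per group.

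Detectable difference in SD units = (z for alpha + 0.842) × √(2 / effective n), with z = 1.960 at 0.05 and 2.394 at 0.05/3:

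| Design effect | One primary, alpha 0.05 | Three primaries, alpha 0.05/3 each |
|---|---|---|
| 1.7 | 2.802 × √(2/110.1) = 0.378 | 3.236 × √(2/110.1) = 0.436 |
| 1.324 | 2.802 × √(2/141.3) = 0.333 | 3.236 × √(2/141.3) = 0.385 |

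Power at two-sided 0.05 for assumed true differences:

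| True difference (SD) | Design effect 1.7 | Design effect 1.324 |
|---|---|---|
| 0.2 | 32% | 39% |
| 0.3 | 60% | 71% |
| 0.4 | 84% | 92% |
| 0.5 | 96% | 99% |

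Depending on a difference that the article does not state, power runs from poor to ample.

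**The case against.** The strongest reply is that abstinence is not foreign to the plan. Partial or total abstinence in 2.4 and reduced consumption or abstinence in 3.1.1 read naturally as one binary construct. Section 2.3 plans a Chi-square test and binary logistic regression, which suit it. Section 2.2.2 checks at 12 months whether the behaviour change has held, and SDU per day is collected at every visit. An exact threshold may stand in the full protocol, in an analysis plan or in the prior study. This is largely right, and it narrows the point: the sizing endpoint may well be derivable from a declared outcome. It does not remove the point, because that endpoint is still not declared, and the three that are declared carry no power statement.

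A reader might infer more, and the article does not support it:

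- **That the trial is underpowered for its primaries.** No inputs are given from which this could be shown.
- **That 3.1.1 introduces a further, different endpoint.** It plausibly restates the one in 2.4.
- **That a success rate could be picked after the data are seen.** The documents that would fix the definition are not at hand, so this is not shown.
- **That regression to the mean undermines a success rate.** Patients are selected for high consumption, but the effect acts in both arms and does not by itself bias a randomised comparison.

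The SD-based figures also have a limit: frequency of more than 6 SDU in a day may be ordinal, and they may not apply to it.

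**Conclusion.** The mismatch between sections 2.4 and 2.5.1 stands. The calculation is correct for abstinence at 37% against 20%, but the 80% it delivers is attached to no declared patient primary. The supportable statement is that power for those primaries is not established, not that it is below 80%.

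As a guide to size, for one primary analysed as a mean, 80% power needs about 0.38 SD at the stated design effect, or about 0.33 SD at the planned 7 to 8 patients per professional. If alpha is split over three primaries, these become about 0.44 and 0.385 SD. The figures assume an ICC of 0.05, 5% loss, equal cluster sizes and no gain from baseline adjustment. Whether such differences are expected cannot be judged from the article.

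**What to change.** Either of two changes would settle it.

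**(a) Declare the powered endpoint.** In 2.5.1, list partial or total abstinence at 12 months as the single primary patient outcome. Define it in advance as in the prior study that supplied 37% and 20%, deriving it from the SDU and AUDIT data already scheduled at 12 months. If the definition has to differ from that study's, the two rates must be re-justified, since otherwise the sample size would again rest on another endpoint. Move the present three primaries to secondary, and use the same definition in 2.4, 3.1.1 and the abstract.

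**(b) Power a declared endpoint.** Keep one of the three as the primary, for example AUDIT total at 12 months. Restate 2.4 as 80% power for about 0.38 SD at design effect 1.7, giving the assumed SD so that the difference can be read in AUDIT points. If the design effect is recomputed for 7 to 8 patients per professional at ICC 0.05, the figure is about 0.33 SD, and the 1.7 in 2.4 must change with it. If all three stay primary with alpha split, state about 0.44 SD at 1.7, or 0.385 SD at about 1.32.

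The cost is wording in 2.4, 2.5.1, 3.1.1 and the abstract, and an updated outcome listing. The downside is that some current primaries become secondary. Option (a) keeps 394 if the prior definition is used and can be derived from the scheduled data; option (b) needs an SD that the article does not give.

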### 2.5. Outcome measurements

#### 2.5.1. Dependent variables (endpoint or outcome)

**-Variables measured in healthcare professionals:**

The following variables will be measured to assess the impact of the training program on participants:

Primary outcomes will be the MI evaluation based on the EVEM scale (22) the patient-healthcare professional relationship based on the CICAA scale (28), and the professional awareness of alcohol use and attitude toward its approach.

Secondary outcomes will be the professional empathy based on Jefferson scale (23), and previous training of healthcare providers in MI.

**-Variables measured in patients with risky alcohol use:**

To assess the effectiveness of interventions, the main outcome variables will be the number of SDU in a typical day, the frequency of more than 6 SDU/day, and the total score of the AUDIT (21) questionnaire. All these variables will be considered as primary outcomes.

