**Materials and methods:**

A cluster-randomized, two-arm parallel, multicenter, open-label, controlled clinical trial. Fifty PC healthcare professionals from the province of Córdoba (Spain) will be randomized to one of the two study groups: (1) Experimental Group (EG): MI-based approach; (2) Control Group (CG): Usual care based on health advice. EG intervention: Professionals will receive a training program focused on MI, consisting of a training workshop and the use of pre- and post-workshop questionnaires to measure knowledge and skills acquired, as well as the degree of empathy, with a videotape of the health professionals with standardized patients, before and after the workshop, and subsequent training feedback. CG intervention: Workshop on the management of risky alcohol use based on health advice; participants will also complete the pre-and post-workshop questionnaires and be videotaped. Study population: Patients ≥ 14 years old with risky alcohol consumption (28 Standard Drink Units-SDU-/week in men and 17 SDU/week in women) or excessive alcohol use (≥ 6 SDU in men or ≥ 4 SDU in women, in less than 2 h). It would be necessary to include 110 subjects/group to find a difference of 20% between the percentage of patients in abstinence between EG (37%) and CG (20%), alpha error of 5%, and statistical power of 80%. Assuming a loss rate of 5% and the cluster design effect, the number of subjects to be recruited is estimated at 197/group. The follow-up period will be 12 months. The primary outcome variables will be the self-reported alcohol use level and the Alcohol Use Disorders Identification Test (AUDIT) questionnaire score.

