#### 2.2.1. Follow-up period

The follow-up period for each patient will be 12 months, with 5 scheduled visits (initial, after 1, 3, 6, and 12 months).

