#### 2.2.2. Data collection and management

Measurements will be obtained as follows: (1) Pre-intervention: Initial or baseline data collection; (2) Intervention: Data will be collected at 1, 3, and 6 months after the baseline visit; (3) Postintervention: twelve months after recruitment, the patient will be interviewed to assess whether he/she maintains his/her status regarding the change of behavior over time.

The data obtained will be recorded in the data collection notebooks and sent online to the study coordinator for further processing, cleaning, and statistical analysis.

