**-Variables measured in patients with risky alcohol use:**

The following variables will be measured in patients with risky alcohol use: age, sex, previous interventions, marital status, education level, place of residence, weight, height, body mass index (BMI), associated diseases, hygiene-dietary habits (such as smoking–number of cigarettes per day- and coffee consumption–number of coffees per day), and stage of change according to Prochaska and DiClemente’s Transtheoretical Model (18). We will also ask participants their opinion about their own alcohol consumption and its consequences in health through an open-ended question. Table 1 shows the variables that will be measured in participants at each follow-up visit.

**TABLE 1 T1:** Variables to be measured at each follow-up visit.

Variables	Follow-up visits				
	**Baseline visit**	**1-month visit**	**3-month visit**	**6-month visit**	**12-month visit**
Socio-demographic characteristics	x				
Clinical measures: weight, height, body mass index (BMI), associated diseases, hygienic-dietary habits (smoking and coffee consumption).	x				
Alcohol consumption opinion	x	x	x	x	x
Standard drink units (SDU)/day of alcohol consumption	x	x	x	x	x
AUDIT questionnaire	x		X	x	x
Scale for the assessment of the motivational interview (EVEM)	x		x	x	
Stage of change regarding alcohol consumption	x	x	x	x	x

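### Three patient outcomes are all primary at an unadjusted two-sided 5% level; if any one suffices, the family-wise error is about 8–14%

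*Protocol article*

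**What the plan says.** - **Outcomes.** Section 2.5.1, on patients: "the main outcome variables will be the number of SDU in a typical day, the frequency of more than 6 SDU/day, and the total score", where the score meant is the AUDIT total. It then adds: "All these variables will be considered as primary outcomes". It gives no ranking and no rule for combining the three.
- **Test level.** Section 2.3: "bilateral comparisons were used, and a value of *p* ≤ 0.05 will be considered". It mentions no adjustment for several primary outcomes.
- **Visits.** Section 2.2.1 sets a 12-month follow-up "with 5 scheduled visits (initial, after 1, 3, 6, and 12 months"). Table 1 lists SDU/day at all four post-baseline visits and AUDIT at 3, 6 and 12 months. Frequency of more than 6 SDU/day has no row of its own.
- **Role of month 12.** Section 2.2.2 labels months 1, 3 and 6 as the intervention phase. Of the post-intervention measurement it says: "twelve months after recruitment, the patient will be interviewed to assess whether he/she maintains his/her status". It does not call this the primary time point.
- **Abstract.** "The primary outcome variables will be the self-reported alcohol use level and the Alcohol Use Disorders Identification Test (AUDIT) questionnaire score".
- **Sample size.** Section 2.4 uses one 5% alpha, 80% power and 37% versus 20% in partial or total abstinence. Abstinence is not one of the three primary outcomes.

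**The concern.** With three outcomes of equal rank and one 5% threshold applied to each, nothing in the text prevents a significant result on just one of them from being reported as a positive primary result. The chance that at least one of three true null hypotheses is rejected is then above 5%, although 5% is the only error rate the article gives. Because no visit is explicitly named as decisive, there is also room to choose the visit.

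What is at stake is the strength of the main claim. A reader of the results could not tell a pre-specified finding from the best of several, and the choice cannot credibly be made once the data have been seen.

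**Working it through.** **1. The plan's own figure.** Inputs from section 2.4: 37% and 20%, alpha 5%, power 80%, two-sided as in section 2.3. The mean proportion is (0.37 + 0.20)/2 = 0.285.

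n = [1.960·√(2·0.285·0.715) + 0.842·√(0.37·0.63 + 0.20·0.80)]² / 0.17² = [1.960·0.638 + 0.842·0.627]² / 0.0289 = 109.5, so **110/group**.

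The design effect is 1 + (15 − 1)·0.05 = 1.7, and 220·1.7/0.95 = 393.7, so **394 (197/group)**. Both figures are reproduced. They correspond to a single two-sided 5% test.

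**2. Family-wise error for three outcomes at one visit.** Inputs: three outcomes (section 2.5.1), each tested two-sided at 0.05 (section 2.3). Assumptions: any one success counts, each test holds its nominal level, and the test statistics are normal with a common correlation r.

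- Independent: 1 − 0.95³ = 0.1426.
- Correlated: 1 − P(all three |Z| ≤ 1.960), by numerical integration and by simulation of 1,000,000 draws. The two agree within simulation error.

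| Assumed r | Family-wise error |
|---|---|
| 0 | 14.3% |
| 0.3 | 13.6% |
| 0.5 | 12.5% |
| 0.7 | 10.9% |
| 0.8 | 9.8% |
| 0.9 | 8.4% |

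The article gives no correlation. Section 2.2 says that AUDIT includes items on usual amount and on binge frequency, so the outcomes overlap and positive correlation is expected. The high values of r therefore belong in the range.

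**3. What control would cost.** Splitting alpha gives 0.05/3 = 0.0167 per outcome, with critical value 2.394. If the tests are independent, the family-wise error is 1 − (1 − 0.0167)³ = 4.9%. With 37% versus 20% as a stand-in effect:

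- Power at 110/group: Φ[(0.17·√110 − 2.394·0.638)/0.627] = **65.8%**. The same formula with 1.960 gives 80.2%.
- Size for 80% power: **147/group**, and 147·1.7/0.95 = 263.1, so about **264/group** to recruit against 197.

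The 65.8% applies to one outcome judged at 0.0167. Holm and Hochberg do no worse than this for each outcome, and they do better when the other outcomes also show an effect.

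**The case against.** The strongest reply is that the article fixes no success rule at all. Inflation arises if any one outcome suffices. If all three had to succeed, there would be none. The decision rule, the adjustment and the time point could also sit in an analysis plan that is not shown. This limits how the point can be put, but does not remove it. The article itself declares three equal primary outcomes and sets one uniform threshold, and an adjustment added later would leave the power statement in section 2.4 without support.

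Three stronger readings are tempting, and the text does not carry them.

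- **Every visit is tested.** A reader might infer a test of each outcome at each visit, and a much larger error rate. Section 2.2.1 and Table 1 schedule measurements, not tests. Carrying the last observation forward (section 2.3) and the post-intervention label (section 2.2.2) both point towards a 12-month comparison. Nor can a count of 11 tests be supported: it needs heavy-day frequency at month 1, which Table 1 does not list, and AUDIT, which holds the binge item, is not scheduled then. The error would rise if several visits were tested, but the text neither states this nor rules it out.
- **11% is the minimum.** It is not. Correlations of 0.8–0.9 give 8–10%.
- **The abstract contradicts section 2.5.1.** Its phrase on self-reported use can fairly be read as shorthand for the two consumption measures. This is mainly condensation and calls for aligned wording.

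It is also fair to say that the 5% in section 2.4 does not belong to any of the three primary outcomes, since it is spent on abstinence.

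**Conclusion.** The point holds in limited form. As written, three equal primary outcomes are each judged at two-sided p ≤ 0.05, with no adjustment, no requirement that all succeed and no explicitly named primary time point. If any one outcome at a single visit can support the claim, the family-wise error is about 8–14%.

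That range rests on assumed correlations from 0 to 0.9 and on each test holding its nominal 5%. It leaves out the separate primary outcomes for professionals in section 2.5.1. It also leaves out any effect of clustering on the tests named in section 2.3, which do not mention it. Over the whole range the error stays above 5%.

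**What to change.** **Preferred.** In section 2.5.1, name one primary patient outcome at 12 months. Make the other two outcomes, and all 1-, 3- and 6-month results, secondary. Alpha stays at 5% with no adjustment. Section 2.4 is built on abstinence, so the power for the chosen outcome must be stated.

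**Alternative.** Keep all three as primary, test them at 12 months only, and apply Holm or Hochberg at an overall 5%. Under Holm the smallest p-value must meet 0.0167 before anything can be claimed. Under Hochberg the same threshold applies if only one outcome is significant. On the stand-in effect, power per outcome at 110/group can fall from about 80% to about 66%, so the power in section 2.4 must be restated or the sample size raised.

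**Either way.** Align the abstract's wording with section 2.5.1. The text change is one paragraph across sections 2.5.1 and 2.3 and needs no new data. The real cost lies in the power statement, and only the alternative loses power through the adjustment itself.
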